# Prevention of exacerbations in patients with COPD and vitamin D deficiency through vitamin D supplementation (PRECOVID): a study protocol

**DOI:** 10.1186/s12890-015-0101-4

**Published:** 2015-09-23

**Keywords:** Chronic obstructive pulmonary disease, Exacerbation, Vitamin D, Immunomodulation, Physical function, Randomised controlled trial

## Abstract

**Background:**

Vitamin D is well known for its function in calcium homeostasis and bone mineralisation, but is increasingly studied for its potential immunomodulatory properties. Vitamin D deficiency is a common problem in patients with COPD. Previous studies have not demonstrated a beneficial effect of vitamin D on exacerbation rate in COPD patients. However, subgroup analyses suggested protective effects in vitamin D deficient patients. Our objective is to assess the effect of vitamin D supplementation on exacerbation rate specifically in vitamin D deficient COPD patients.

**Methods/Design:**

We will perform a randomised, multi-center, double-blind, placebo-controlled intervention study. The study population consists of 240 COPD patients aged 40 years and older with vitamin D deficiency (25-hydroxyvitamin D concentration < 50 nmol/L). Participants will be recruited after an exacerbation and will be randomly allocated in a 1:1 ratio to receive vitamin D3 16800 IU or placebo orally once a week during 1 year. Participants will receive a diary card to register the incidence of exacerbations and changes in medication during the study period. Visits will be performed at baseline, at 6 months and at 12 months after randomisation. Participants will undergo spirometry, measurement of total lung capacity and assessment of maximal respiratory mouth pressure. Several physical performance and hand grip strength tests will be performed, questionnaires on quality of life and physical activity will be filled in, a nasal secretion sample and swab will be obtained and blood samples will be taken. The primary outcome will be exacerbation rate.

**Discussion:**

This study will be the first RCT aimed at the effects of vitamin D supplementation on exacerbation rate in vitamin D deficient COPD patients. Also, in contrast to earlier studies that used infrequent dosing regimens, our trial will study effects of a weekly dose of vitamin D supplementation. Secondly, the immunomodulatory effects of vitamin D on host immune response of COPD patients and underlying mechanisms will be studied. Finally, the effects on physical functioning will be examined.

**Trial registration:**

This trial is registered in ClinicalTrials.gov, ID number NCT02122627. Date of Registration April 2014.

## Introduction

Chronic obstructive pulmonary disease (COPD) is characterized by a persistent airflow limitation and an abnormal inflammatory response of the airways. COPD is predicted to be the third worldwide cause of mortality by 2020 [1]. Exacerbations in COPD determine disease-associated morbidity and mortality [2]. Patients with frequent exacerbations have a more rapid decline in lung function, worse quality of life and decreased exercise performance. Yet, effective treatment alternatives to prevent exacerbations are still lacking.

Vitamin D deficiency is highly prevalent in patients with COPD [3, 4]. Traditionally, vitamin D is associated with bone health. The discovery of the presence of vitamin D receptors (VDR) in many other cells, such as monocytes, macrophages, muscle cells and endothelial cells, has elicited hypotheses of direct vitamin D effects on these cells. These hypotheses are further strengthened by local 25-hydroxyvitamin D-1-alpha-hydroxylase activity, which converts the inactive 25-hydroxyvitamin D (25(OH)D) to the active 1,25-dihydroxyvitamin D (1,25(OH)_2_D), in many of these cells. The presence of vitamin D receptors on immune cells [5] and the high prevalence of vitamin D deficiency among COPD patients has given rise to the hypothesis that vitamin D might have a potential effect in preventing exacerbations in patients with COPD [6].

### Vitamin D and the immune system

There is a large body of evidence being generated *in vitro* and *in vivo* to demonstrate that vitamin D influences the innate and adaptive immune system. 1,25(OH)_2_D is the active form of vitamin D that binds to the VDR, thereby influencing the expression of more than 200 genes. VDR is expressed on a range of immune cells such as macrophages, dendritic cells, and CD4-positive T lymphocytes [5]. In the innate immune system vitamin D modulates Toll-like receptor (TLR)-induced immune responses through inhibition of the NF-κB-pathway and appears to improve antimicrobial defences in general [7, 8]. Vitamin D is capable of inducing endogenous expression of the antimicrobial peptides (AMP) such as cathelicidin. This has been reported in monocytes, macrophages, keratinocytes and in lung epithelial cells [9, 10]. Because AMPs have been found in multiple experimental systems to be essential for defence against a variety of microbial infections, it has been hypothesised that vitamin D can enhance resistance to infections [11]. In addition, vitamin D seems capable of modifying the function of cells classically associated with adaptive immunity whereby activation of VDR downregulates autoimmunity by promoting the differentiation of T-cells into regulatory T-cells [12].

### Vitamin D and pulmonary infections

Vitamin D might influence the development and course of tuberculosis. Patients with low 25(OH)D concentrations have a higher risk of active tuberculosis and vitamin D supplementation may shorten the duration of disease [13]. It is also known that patients with rickets more frequently suffer from airway infections and pneumonia [14]. Several prospective cohort studies in the general population show that lower levels of 25(OH)D are related to increased risk of respiratory infections [15, 16]. A trial with Japanese schoolchildren during the influenza season demonstrated that, compared to placebo, vitamin D supplementation lowered the incidence of influenza A infections [17]. Trials assessing effects of vitamin D supplementation on prevention of respiratory infections in the general adult population have shown conflicting results, which may partly be attributed to differences in prevalence of vitamin D deficiency at baseline and rise of serum 25(OH)D levels during treatments [18, 19].

### Vitamin D and COPD

Patients with COPD are characterised by an abnormal inflammatory response of the airways. Viral and bacterial infections are important triggers of exacerbations and contribute to its progression. Thus, potential effects of vitamin D on the immune system pose an attractive mechanism for the treatment of COPD. Also, in some [20, 21], but not all [22] studies in the general population serum 25(OH)D is positively associated with lung function. Vitamin D deficiency is present in 40–80 % of patients with COPD and is related to disease severity [3, 4]. Recent cohort studies, however, did not show a relationship between 25(OH)D levels and exacerbation rate [23, 24], although these studies had limited statistical power to rule out effects of vitamin D deficiency.

In addition to exacerbations and lung function, skeletal muscle dysfunction in COPD patients contributes to poor exercise capacity, decreased quality of life and increased mortality [25, 26]. In COPD patients, vitamin D deficiency is related to impaired physical performance [27]. In healthy adults, positive effects of vitamin D supplementation have been demonstrated on muscle function and physical performance in particular in older and frail individuals [28, 29].

### RCTs vitamin D supplementation in COPD

Few studies have been performed on the effects of vitamin D supplementation in patients with COPD. In the trial performed by Lehouck et al. [30] vitamin D supplementation did not reduce the incidence of exacerbations. However, in a post-hoc analysis of a subgroup of severely vitamin D deficient patients (25(OH)D concentration < 25 nmol/L), vitamin D supplementation decreased the exacerbation rate. In a very recent multi-center trial by Martineau et al. [31] vitamin D protected against moderate to severe exacerbations in a pre-specified subgroup of vitamin D deficient (25(OH)D concentrations < 50 nmol/L) participants, but not in the study population as a whole.

Two studies have been performed assessing the effect of vitamin D supplementation on physical performance in patients with COPD. A pilot RCT did not show effects of vitamin D supplementation on physical performance, but was limited by the small number of 36 participants and short follow-up of 6 weeks [32]. Also, the study was not specifically aimed at patients with vitamin D deficiency. In the aforementioned RCT by Lehouck et al. a post-hoc subgroup analysis of 50 participants following a rehabilitation programme during the trial was performed [33]. Participants receiving vitamin D supplementation had significantly larger improvements in inspiratory muscle strength and peak exercise tolerance, but not in quadriceps strength and 6-min walking distance. However, this study had limited statistical power and is only applicable for patients following a rehabilitation programme. These findings justify a well-designed RCT to study effects of vitamin D supplementation on muscle strength and physical performance.

Little is known about the total dose and dose interval needed for extra-skeletal effects of vitamin D. In the study of Lehouck et al. [30] participants received a monthly dose of 100.000 IU. In the study of Martineau et al. [31] participants received 120.000 IU every two months. A large dose interval improves compliance but might also cause fluctuating levels of vitamin D metabolites [34]. In two RCTs assessing the effect of vitamin D supplementation on falls and fractures, an increase of fall and/or fracture incidence were shown using annual high dose supplementation [35, 36]. While the mechanism by which vitamin D might cause an increase in falls remains uncertain, several authors suggest it is the dosing interval rather than the total dose that determined these outcomes [37]. These results emphasize the need for an RCT studying a more frequent dosing regimen of vitamin D.

In the present study we aim to study the effects of vitamin D supplementation on exacerbation rate in COPD patients with vitamin D deficiency. In addition, we will also assess the effects of vitamin D on several measures of physical performance. In our trial, we will administer a weekly dosing regimen in contrast to earlier studies, which used larger dosing intervals.

## Methods

### Study design and participants

The study is designed as a randomised double-blind, multi-center, placebo-controlled trial, with an intervention (*n* = 120) and a control group (*n* = 120). The study population consists of COPD patients with GOLD stages II-IV. Participants will be included if they have a vitamin D deficiency (25(OH)D concentrations <50 nmol/L) and a recent exacerbation of COPD. The eligibility criteria are described in Table 1. Participants will be recruited if they present with an exacerbation of COPD at the outpatient clinic or emergency ward. Screening serum 25(OH)D concentration will be measured during the exacerbation period. Inclusion and randomisation will take place 6–8 weeks after recruitment or at a later time point as soon as the participant has recovered. An exacerbation is defined as sustained worsening of respiratory symptoms during 48 h requiring oral corticosteroid, antibiotic or combination treatment that was initiated by a physician [38]. Convalescence is defined as recovery to the stable state. The recruitment will start in three academic hospitals and five peripheral hospitals in the surroundings of the academic centers. Study visits will be performed at baseline (t = 0), 6 months (t = 6) and 12 months (t = 12) after randomisation as depicted in Fig. 1. Participants will be contacted by telephone at 2, 4, 8 and 10 months The study is approved by the Medical Ethics Committee of the VU University Medical Center, Radboud University Medical Center and Leiden University Medical Center. Written informed consent will be obtained from all participants.

**Table 1 Tab1:** Eligibility criteria for the PRECOVID trial

Inclusion criteria	Exclusion criteria
Vitamin D deficiency (serum 25(OH)D < 50 nmol/l)	Severe vitamin D deficiency (serum 25(OH)D <15 nmol/l),
Postbronchodilator FEV_1_/FVC < 0.70, FEV_1_ < 80 % and diagnosis COPD confirmed by a physician	Use of a supplement containing more than 400 IU vitamin D per day
Recent COPD exacerbation	Use of maintenance dose oral corticosteroids
≥10 packyears of smoking	Diagnosed asthma
Age ≥ 40 years	Diagnosed osteoporosis
Written informed consent	Self-reported history of hypercalcaemia or nephrolithiasis
Ability to comply with all study requirements.	Self-reported presence of sarcoidosis
	Diagnosed chronic kidney disease stage 4 or higher (eGFR ≤ 29 ml/min/1.73 m2)
	Interfering malignant diseases
	Life expectation of less than 1 year on the basis of concurrent disease
	Current participation in a clinical rehabilitation program
	Pregnant or lactating women, or subjects who intend to become pregnant within the study period
	Potentially unreliable patients and those judged by the investigator to be unsuitable for the study
	Serious mental impairment i.e. preventing to understand the study protocol or comply with the study aim

*25(OH)D* 25-hydroxyvitamin D, *FEV*
_*1*_ Forced Expiratory Volume in one second, *FVC* Forced Vital Capacity, *eGFR* estimated Glomerular Filtration Rate with the MDRD formula

**Fig. 1 Fig1:**
[figure not shown]
Flowchart of study procedures during the PRECOVID trial. Randomisation will take place within 6-8 weeks after an exacerbation. During the study period of one year three study visits and four telephone contacts will take place. MIP: Maximal inspiratory pressure; MEP: Maximal expiratory pressure; TLC: Total lung capacity

### Intervention

The participants will receive either vitamin D 16800 IU (3 tablets of 5600 IU) or a matching placebo (3 placebo tablets) orally once a week during 12 months in accordance with the randomisation. The study medication will be prepared under supervision of the clinical pharmacy of the VU University Medical Center. Participants will be asked to return the study medication that is left over and these tablets will be counted as a measure for compliance. Participants are allowed to use a maximum of 400 IU vitamin D a day during the study, as this is the recommended daily intake by the Dutch Health Council. Participants will be asked about their usual intake of dairy products. Participants are advised (according to the advice of the Dutch Health Council) to increase their intake to a level corresponding with 1000 mg calcium per day. If this is not feasible, it will be advised to use calcium supplements to a total calcium intake of 1000 mg/day during the study.

### Randomisation and masking

For treatment allocation in this trial, we will apply the sequential balancing method with study center as the first step in the balancing algorithm, followed by gender, age and current smoking. These variables are (potential) prognostic factors and thus should be balanced over the treatment arms. Pharmacists of the VU University Medical Center, who are independent from the clinical research team, will randomly assign participants by using a computer-generated randomisation list and will prepare the study medication. After the last participant finishes the trial masking will continue until after the data analyses.

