#### Secondary outcomes

Time to first exacerbation and hospitalisation will be assessed with Kaplan–Meier curves and Cox proportional hazard models. Dichotomous secondary outcomes will be analysed with logistic regression models and continuous secondary outcomes with analysis of covariance. All analyses will be adjusted for the variables included in the balancing algorithm for randomisation, i.e. study center, gender, age and current smoking. Because of the exploratory nature of the analyses, no correction will be made for the multiple analyses. All analyses of the trial will use the intention-to-treat population, defined as all randomly assigned participants who received at least 1 dose of study medication. A per-protocol analysis will be performed on those participants with a good compliance i.e. obtaining a serum 25(OH)D concentration above the 20^th^ percentile after 12 months. Also, a subgroup analysis will be performed in participants with a baseline serum 25(OH)D concentration of 25 nmol/L or less.

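### 25(OH)D is missing from the balancing list and so from the model covariates; adding the baseline value as a covariate is a nearly free improvement, and its absence is not an error

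*Protocol article*

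**What the plan says.** Protocol article, Randomisation and masking: allocation uses sequential balancing with "study center as the first step in the balancing algorithm, followed by gender, age and current smoking". The reason given is that "These variables are (potential) prognostic factors and thus should be balanced over the treatment arms".

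Statistical analysis, Primary outcome and Secondary outcomes: both sections define the adjustment set as the variables in the balancing algorithm and list the same four. A variable left out of the algorithm is therefore also left out of the stated models.

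Study design and participants, with Table 1: eligibility requires 25(OH)D below 50 nmol/L and excludes values below 15 nmol/L. On timing, "Screening serum 25(OH)D concentration will be measured during the exacerbation period", and "Inclusion and randomisation will take place 6–8 weeks after recruitment or at a later time point as soon as the participant has recovered". A value is thus on file for everyone before allocation.

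Secondary outcomes also plans that "a subgroup analysis will be performed in participants with a baseline serum 25(OH)D concentration of 25 nmol/L or less". No expected size is given for this subgroup. The article does not say whether the baseline value is the screening sample or a new one at t = 0.

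Vitamin D and COPD: "Vitamin D deficiency is present in 40–80 % of patients with COPD and is related to disease severity". The same paragraph adds that recent cohort studies showed no relation between 25(OH)D and exacerbation rate, and that these studies had limited power.

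**The concern.** The article's test for a balancing variable is low: a potential prognostic factor is enough. A variable said to track disease severity can meet that test. 25(OH)D is also what the trial rests on. It sets eligibility, and benefit in deficient subgroups of two earlier trials is the reason for the study. One of those subgroups, below 25 nmol/L, nearly matches the planned cut.

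Because the adjustment set is copied from the balancing list, one omission leaves 25(OH)D uncontrolled in both design and model. Two things could follow. The low-25(OH)D subgroup could split unevenly between arms and lose precision. The arms could also differ by chance in their share of such patients, and if those patients exacerbate more often, the primary rate ratio would move without the stated adjustment correcting it. The question is how large either effect can be.

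**Working it through.** The plan gives no figure on this point, so there is none to reproduce.

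**Inputs**
- From the article: 240 participants, 120 per arm; assumed rates 2.45 and 3.45 per patient-year; 5% significance, taken as two-sided.
- Assumed: 20–30% of participants at or below 25 nmol/L, so m = 48 or 72. Shares of 10% (m = 24) and 40% (m = 96) are added to show the range.
- Also assumed: membership of this stratum is unrelated to the four balanced factors. With fixed arms of 120, the number x of stratum patients in one arm is then hypergeometric (240, m, 120).

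**1. Difference between arms in the share of low-25(OH)D patients**

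The difference is |x − (m − x)|/120. It reaches 10 points when |2x − m| ≥ 12.
- m = 48: x ≤ 18 or x ≥ 30, probability 7.5%.
- m = 72: x ≤ 30 or x ≥ 42, probability 12.1%.

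**2. Split within the subgroup**

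A 60:40 or worse split means max(x, m − x)/m ≥ 0.6.
- m = 48: 29 or more in one arm, probability 14.6%.
- m = 72: 44 or more in one arm, probability 3.4%.
- For the wider range: 28% at m = 24 and 1% at m = 96.

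A binomial with probability 0.5 would overstate these figures, because it ignores the fixed arm sizes.

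**3. What an uneven split costs**

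Efficiency relative to an exact 1:1 split is 4x(m − x)/m². A 60:40 split keeps 4 × 0.6 × 0.4 = 96%. Averaged over the hypergeometric, this is 1 − (240 − m)/(239m):
- m = 48: 1 − 192/(239 × 48) = 98.3%.
- m = 72: 1 − 168/(239 × 72) = 99.0%.

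Subgroup power at the protocol's rates is Φ(1/√(2.45/n₁ + 3.45/n₀) − 1.96). For an exact 1:1 split at m = 48, 1/√(5.90/24) = 2.017, so power is Φ(0.057) = 52.3%.

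| m | Power, exact 1:1 | Power, average over chance splits | Mean efficiency |
|---|---|---|---|
| 24 | 29.7% | 28.8% | 96.2% |
| 48 | 52.3% | 51.6% | 98.3% |
| 72 | 69.5% | 69.1% | 99.0% |
| 96 | 81.4% | 81.1% | 99.4% |

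The counts may be more variable than Poisson. With the variance doubled, balanced power falls to 29.7% (m = 48) and 41.6% (m = 72), and the average loss from chance splits is 0.3–0.5 points over the whole range of m. Subgroup power is low because the subgroup is limited in size, and balancing cannot change that.

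**4. Effect on the primary rate ratio**

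Suppose the low stratum has f times the rate of the others (assumed; the article gives no figure) and the arms hold 25% and 15% of such patients. The unadjusted rate ratio is then multiplied by (1 + 0.25(f − 1))/(1 + 0.15(f − 1)).
- f = 1.2: 1.050/1.030 = 1.019.
- f = 1.5: 1.125/1.075 = 1.047.

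The shift is about 2–5%, or 0.019–0.045 on the log scale. The pure Poisson standard error of the log rate ratio with 120 per arm is √(1/(120 × 2.45) + 1/(120 × 3.45)) = 0.076. The shift is therefore about a quarter to 0.6 of a standard error, and an imbalance of this size or more arises with probability of only about 8–12%.

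**The case against.** The strongest reply is that nothing here is wrong. The balancing list follows the article's own criterion, and for the primary outcome the article reports that cohorts did not show a relation with 25(OH)D. Effect modification is not the stated reason for balancing, and a valid subgroup comparison does not need it. Eligibility already narrows the range to 15 to below 50 nmol/L. The subgroup is one analysis in a section that calls its analyses exploratory. A fifth factor could loosen balance on the others. Further covariates are often settled in the statistical analysis plan, which is not shown.

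Most of this stands, and it removes any claim of error. Two parts are weaker. The cohort evidence is described as underpowered, so the article leaves the question open, and a potential factor is all its criterion asks for. The article also does not leave the covariates open: it states the adjustment set as exactly the balancing variables.

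A reader might infer that the subgroup comparison is confounded by severity. The documents do not support that. Patients at or below 25 nmol/L are still randomised, so any difference in severity between arms is a chance imbalance. Equal numbers per arm would not balance severity inside the stratum either. A reader might also call the subgroup small, but the article gives no size.

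Nor can balancing on the screening value be said to remove subgroup imbalance. The subgroup uses a baseline value, and the article does not say that this is the sample taken during the exacerbation, at least six weeks before randomisation.

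**Conclusion.** The point holds as a low-cost improvement. The balancing list, and through it the adjustment set, omits a variable that is known for everyone before randomisation, may be prognostic and defines the planned subgroup. Validity is not threatened.

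At an assumed 20–30% share, a between-arm difference of 10 points or more has probability about 8–12%, and a 60:40 or worse subgroup split about 15% to 3%. Average efficiency in the subgroup falls by 1–2% (up to 4% if the share is only 10%), and power by less than one point. A 10-point imbalance would move the primary rate ratio by about 2–5% only if the low stratum has a 1.2- to 1.5-fold rate. Both the share and the rate multiple are assumptions. If 25(OH)D is unrelated to exacerbation rate, the shift is nil.

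**What to change.** Prespecify baseline 25(OH)D as a further covariate, preferably continuous, in the primary Poisson model and in the secondary models. State which sample, screening or t = 0, is meant by baseline, and use that sample for both the covariate and the 25 nmol/L subgroup. The cost is one model term and one sentence. The screening value is already collected, allocation is untouched, and the change can be made after randomisation has begun provided it is fixed before unmasking. It also avoids a later argument about adjustment should the arms differ on the trial's defining variable.

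Adding 25(OH)D (at or below versus above 25 nmol/L) to the sequential balancing algorithm is optional and only sensible before randomisation starts. It costs one more input and possibly slightly looser balance on the other factors, for an average gain of under one point of subgroup power.
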